**Figure 1. F1:**
[figure not shown]
Study procedure.

#### Withdrawal Criteria

The participants may be withdrawn from the trial under any of the following circumstances: (1) any adverse event or adverse reaction (AR), (2) voluntary withdrawal by the participant, (3) violation of inclusion or exclusion criteria, or (4) noncompliance with the treatment regimen (a minimum of 80% compliance is required to continue participating in the study).

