##### Examination of the Patient

Patients unfit for nasal oil administration will be excluded. Informed consent will be obtained, and the patients will be instructed to brush their teeth and clean their mouths.

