### Data Collection Plan and Management

All the details entered in CRFs will be collected, and each participant will be provided with a unique enrollment number. The signed consent forms, along with the CRFs, will be placed in locked cabinets, and all electronic data will be password protected. Data access will be limited to the principal investigator and coinvestigator during and after the study. For dropouts, 10% of the data will be imputed using proper techniques, and efforts will be made to collect data for at least 1 month after enrollment.

Emergency unblinding will be conducted only if necessary for the participant’s safety or clinical management. If needed, the investigator will follow the emergency unblinding procedure. The allocation will not be revealed to the participant or study personnel unless necessary for patient care. All unblinding events will be recorded in the CRF.

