### Statistical Methods

One-way ANOVA will be applied to compare the means of the 3 groups. If ANOVA indicates a significant difference, post hoc tests will be further applied (eg, the Tukey honestly significant difference test) to identify which group differs. A *P* value of <.05 will be considered statistically significant. Covariates such as age and baseline severity will be considered, and adjustments will be made using analysis of covariance if needed. The analysis will be intention to treat, with missing data handled through multiple imputation. Statistical assistance will be provided by a statistician or someone skilled in statistics. We will use SPSS (version 26; IBM Corp) for statistical analysis.

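### Randomised patients may be withdrawn from the trial, not only from treatment, for adverse events, ineligibility or under 80% compliance, which undermines the intention-to-treat analysis

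*Protocol article*

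**What the plan says.** The protocol article, Withdrawal Criteria, opens: "The participants may be withdrawn from the trial under any of the following circumstances: (1) any adverse event or adverse reaction (AR". The compliance ground is worded as follows: "noncompliance with the treatment regimen (a minimum of 80% compliance is required to continue participating in the study". The remaining grounds are voluntary withdrawal and "3) violation of inclusion or exclusion criteria". No severity threshold is attached to the adverse event ground, and the eligibility ground is not limited to the time before randomisation. Nothing in the section distinguishes stopping treatment from leaving the study.

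Statistical Methods states: "The analysis will be intention to treat, with missing data handled through multiple imputation".

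Data Collection Plan and Management makes two statements on dropouts in one sentence. The first concerns imputation: "For dropouts, 10% of the data will be imputed using proper techniques". The second concerns follow-up: "efforts will be made to collect data for at least 1 month after enrollment".

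The section on adherence strategies has both procedure adherence and capsule consumption checked daily through the 7 treatment days. Outcomes are assessed on days 8, 16 and 32 (Overview of Methods; Table 1).

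**The concern.** An intention-to-treat analysis needs outcomes on all randomised patients, whatever happened to their treatment. Here three of the four withdrawal grounds can be applied by the trial to a patient who still consents, and two of them (adverse events and noncompliance) arise after randomisation and may be consequences of the assigned treatment. Because adherence is judged before the first outcome visit, a patient withdrawn on that ground can leave with no post-baseline outcome.

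Multiple imputation would then have only that patient's baseline and treatment-period records, and other patients' outcomes, to work from. It would be replacing data that could have been collected. The usual missing-at-random assumption is hard to defend when the reason for the gap is a reaction to treatment or failure to complete it.

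Two further defects make the rule hard to apply. Compliance is undefined although the arms have different numbers of procedure sessions. The figure of 10% for imputation does not fit beside Statistical Methods, because the amount of missing data is not known in advance.

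**Working it through.** **1. Timing.** Adherence is judged on days 1 to 7. The first outcome visit is day 8. A patient withdrawn for noncompliance by day 7 can therefore miss all three outcome assessments.

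**2. What the 80% threshold tolerates.** Planned sessions come from Intervention Description and Table 1: 2 in Group A, 7 in Group B, 7 in Group C. Placebo capsules, twice daily for 7 days, give 14 doses in every arm. Compliance = units taken / units planned.

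- By sessions, Group A: one miss gives 1/2 = 50%, below 80%. No miss is tolerated.
- By sessions, Groups B and C: one miss gives 6/7 = 85.7%, above 80%; two give 5/7 = 71.4%, below 80%.
- By capsules, every arm: two missed doses give 12/14 = 85.7%; three give 11/14 = 78.6%. The rule is the same in all arms.
- Sessions and capsules pooled, Group A: one missed session gives 15/16 = 94%, above 80%.

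**3. Chance of breaching the rule if sessions are counted.** The documents give no miss rates. Assume that each session is missed independently with probability p, the same in all arms.

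- Group A: 1 − (1 − p)²
- Groups B and C: 1 − (1 − p)⁷ − 7p(1 − p)⁶

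| Assumed p | Group A | Group B or C | Expected per 20 patients, A against B or C |
|---|---|---|---|
| 2% | 4.0% | 0.8% | 0.79 against 0.16 |
| 5% | 9.8% | 4.4% | 1.95 against 0.89 |
| 10% | 19.0% | 15.0% | 3.80 against 2.99 |
| 15% | 27.8% | 28.3% | 5.55 against 5.67 |
| 20% | 36.0% | 42.3% | 7.20 against 8.47 |

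The arms are treated differently at most rates, but the difference vanishes near 15% and reverses at 20%.

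**4. What lost outcomes cost.** The plan's own figure first, with the inputs in the Sample Size section (SD 0.58, difference 0.526, 1.96 and 0.84):

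n = 2 × (1.96 + 0.84)² × 0.58² / 0.526² = 19.06, rounded up to 20 per group.

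This reproduces the stated 20. The calculation contains no dropout allowance. Pairwise power by normal approximation is Φ(0.526 / (0.58 × √(2/n)) − 1.96):

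- n = 20: 81.8%
- n = 18 (10% lost, assumed): 77.7%
- n = 16 (20% lost, assumed): 72.7%
- n = 14 (30% lost, assumed): 67.0%

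These figures treat lost outcomes as not recovered. They show the loss of information, not the bias.

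**5. The follow-up clause for dropouts.** One month is 28 to 31 days. Counted from enrolment, that minimum covers days 8 and 16 but may stop just short of day 32, when the secondary objective is assessed.

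**The case against.** The best defence is that the protocol does not abandon withdrawn patients. Withdrawal is permitted rather than ordered, follow-up of dropouts is intended for about the length of the trial, and multiple imputation keeps every randomised patient in the analysis. Much of this stands, and it rules out several stronger readings.

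- A reader might infer that patients are removed automatically. The section says that they may be withdrawn; only the 80% minimum is worded as a requirement. Discretion does not cure the problem, since no criteria for exercising it are given.
- A reader might infer that withdrawn patients are dropped from the analysis, so that intention to treat is flatly contradicted. Nothing says so. The weakness lies in the data behind the analysis, not in the analysis set.
- A reader might infer that all outcomes end at withdrawal. The follow-up clause points the other way. It promises only efforts, however, and sits beside a rule that ends participation.
- A reader might infer that the 80% rule always penalises Group A. That requires counting sessions alone, and even then the direction depends on the miss rate. Equal miss rates for 2 visits and for 7 daily visits are themselves an assumption.
- A reader might infer that imputation would flatter the arm that is hardest to tolerate. The documents give no tolerability rates and no imputation model, and the model may properly be left to an analysis plan. No direction of bias can be stated.
- A reader might take "Patients unfit for nasal oil administration will be excluded", in the nasal oil procedure, as an exclusion of patients already assigned to Group C. Fitness for nasal oil is already an inclusion criterion for all patients, so this text largely repeats it and is not relied on here.
- The 10% might be meant as an expected dropout rate. The text does not say so, and the sample size makes no allowance for one.

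**Conclusion.** The concern holds in a limited form. The withdrawal rule lets the trial end the participation of consenting randomised patients, for reasons that may be related to treatment, before any outcome is measured. Multiple imputation and a promise of efforts soften this but do not remove it. That conclusion rests on the text alone and needs no assumption about rates.

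The difference between arms is conditional. It arises if compliance is counted by procedure sessions and is absent if it is counted by capsules. Its size and direction depend on miss rates that the documents do not give. The power figures likewise rest on assumed losses of 10% to 30%. The 10% imputation statement cannot be reconciled with Statistical Methods as written.

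The point deserves action during recruitment, because outcomes not collected cannot be recovered at analysis. The article reports 16 patients recruited by January 2025.

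**What to change.** - In Withdrawal Criteria, separate discontinuing treatment from leaving the study. The grounds for discontinuing treatment are a clinical decision and stay as they are.
- State that every randomised patient is followed and measured on days 8, 16 and 32 whatever their compliance, adverse reaction or eligibility finding, and that only withdrawal of consent ends data collection. Replace the efforts clause in Data Collection Plan and Management with this commitment.
- Use the 80% threshold only to define a supportive per-protocol set, and say what is counted: sessions, capsules or both.
- Delete the statement that 10% of the data will be imputed, so that Statistical Methods alone governs missing data.

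The cost is a short amendment and a few more follow-up contacts, at visits that the study schedule (Table 6) already contains. If outcomes are kept in this way, the sample size of 20 per group need not change on this account. Offsetting a 10% loss by recruitment instead would need 20 / 0.9 = 22.2, that is 23 per group or 69 in total, and would do nothing about bias.

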### Data Collection Plan and Management

All the details entered in CRFs will be collected, and each participant will be provided with a unique enrollment number. The signed consent forms, along with the CRFs, will be placed in locked cabinets, and all electronic data will be password protected. Data access will be limited to the principal investigator and coinvestigator during and after the study. For dropouts, 10% of the data will be imputed using proper techniques, and efforts will be made to collect data for at least 1 month after enrollment.

Emergency unblinding will be conducted only if necessary for the participant’s safety or clinical management. If needed, the investigator will follow the emergency unblinding procedure. The allocation will not be revealed to the participant or study personnel unless necessary for patient care. All unblinding events will be recorded in the CRF.

### Statistical Methods

One-way ANOVA will be applied to compare the means of the 3 groups. If ANOVA indicates a significant difference, post hoc tests will be further applied (eg, the Tukey honestly significant difference test) to identify which group differs. A *P* value of <.05 will be considered statistically significant. Covariates such as age and baseline severity will be considered, and adjustments will be made using analysis of covariance if needed. The analysis will be intention to treat, with missing data handled through multiple imputation. Statistical assistance will be provided by a statistician or someone skilled in statistics. We will use SPSS (version 26; IBM Corp) for statistical analysis.

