**Conclusions:**

This comparative study seeks to establish the most effective treatment among honey thermal microcautery, standard physiotherapy, and *S cordifolia* oil *nasya* for managing frozen shoulder, potentially offering new integrative approaches to treating this condition.

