### Rationale of the Study

The 3 arms in our study were selected considering their unique mechanisms of action to adequately treat FS. Honey thermal microcautery is an Ayurvedic treatment with thermal effects. Standard physiotherapy is the classic gold standard, ensuring a robust comparator. *Sida cordifolia* oil via nasal route was selected considering its efficacy for *vata-kapha* disorders, particularly musculoskeletal diseases. These treatments were selected considering the evaluation and comparison of diverse approaches between modern medicine and traditional medicine toward optimal outcomes.

No study has been published comparing honey thermal microcautery, standard physiotherapy, and *S cordifolia* oil nasal administration. Additionally, no study has explored the use of honey thermal microcautery in FS. Considering these gaps, this study is essential to determine the most effective and safe therapeutic approach for FS, evaluating interventions such as honey thermal microcautery, standard physiotherapy, and *S cordifolia* oil nasal administration to identify treatments that optimize recovery time and minimize associated concerns.

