#### Primary Variable: Abduction Improvement

The primary variable, shoulder abduction improvement, was used to calculate the minimum sample size required for the study, ensuring adequate power to detect a meaningful difference between groups. The primary variable in this study is shoulder abduction improvement, measured as the increase in the range of motion after the intervention. Based on expected differences, variability, significance level, and power, the minimum sample size required was calculated to ensure reliable detection of a meaningful improvement

Where the mean score for abduction in *shudhabala taila nasya* pre=2.23 (as per the study by Revathi et al [22]).

Mom score for abduction in *shudhabala taila nasya* post at follow-up=1.06.

Difference (pretest-posttest)=1.17

SD=0.58.

Considering 45% superiority in the thermal microcautery group=(1.17) × 45 = 0.526

Mean differenсе *δ*=0.526

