Physiotherapy, such as wheel and step ladder exercises, aids in FS by enhancing joint mobility and flexibility. Wheel exercise allows for gradual stretching, whereas step ladder exercise improves shoulder strength and ROM. Together, they facilitate functional recovery and improve ROM. Our hypothesis is that honey thermal microcautery will yield more effective results than standard physiotherapy and *S cordifolia* oil via the nasal route because of its instant and satisfactory benefits. This research may guide future studies, incorporating traditional and modern methods, thus providing a well-rounded treatment for FS. This study seeks to guide clinical decisions by systematically comparing these interventions, enabling the choice of a more effective and individualized treatment for FS. This study compares diverse interventions, uses multidimensional assessment tools, and integrates Ayurvedic principles with modern therapy. It provides a new perspective into honey thermal microcautery; thus, clinicians can fine-tune effective treatments for FS. The limitation of this study is the small sample size, which, while adequate for preliminary insights, may limit the generalizability of the findings. Future studies with larger cohorts and extended follow-up periods are recommended to validate and enhance the applicability of the results. The primary findings will establish that honey thermal microcautery, standard physiotherapy, and *S cordifolia* oil via nasal administration effectively manage FS, ultimately determining which provides the best outcome.

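### The 80% power holds for one unadjusted pair (microcautery vs nasal oil); under the planned ANOVA and Tukey analysis it is about 68% for that pair and lower for the hypothesis that microcautery beats both comparators

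*Protocol article*

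**What the plan says.** **Sizing.** Under Sample Size, the protocol article uses the standard formula for two means with 1.96 and 0.84, that is, two-sided 5% and 80% power. The effect is microcautery's advantage over the nasal-oil abduction change of 1.17: "Considering 45% superiority in the thermal microcautery group=(1.17) × 45 = 0.526". The SD is 0.58. The result, 20 per group, is multiplied by three to give 60. No expected result for physiotherapy is stated, although Rationale of the Study says: "Standard physiotherapy is the classic gold standard, ensuring a robust comparator".

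**Analysis.** Under Statistical Methods: "One-way ANOVA will be applied to compare the means of the 3 groups". It continues: "If ANOVA indicates a significant difference, post hoc tests will be further applied (eg, the Tukey honestly significant difference test) to identify which group differs". The threshold is given once: "A *P* value of <.05 will be considered statistically significant".

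**Claim.** Under Anticipated Findings: "Our hypothesis is that honey thermal microcautery will yield more effective results than standard physiotherapy and *S cordifolia* oil via the nasal route". The conclusions of the abstract say that the study "seeks to establish the most effective treatment among honey thermal microcautery, standard physiotherapy, and" nasal oil.

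**The concern.** The sizing, the test and the claim refer to different things. The sizing covers one pair at an unadjusted 5%. The test covers three groups and then, if Tukey is used, all three pairs with adjustment. The hypothesis needs two pairs to succeed together, and one of them (microcautery vs physiotherapy) has no planning assumption. A reader will take the 80% as the chance that the trial supports its hypothesis if that hypothesis is true, and it is not that.

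The article also does not say what pattern of pairwise results would allow a treatment to be called the most effective. A result in which microcautery beats nasal oil but is not shown to beat physiotherapy is quite likely, and no rule says how it should be worded.

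**Working it through.** **Inputs**

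- From Sample Size: δ = 0.526 (1.17 × 0.45 = 0.5265, recorded as 0.526), SD = 0.58, Zα = 1.96, Zβ = 0.84, n = 20 per arm.
- From Statistical Methods: ANOVA at 5%, then pairwise post hoc tests, with Tukey as the named example.
- Not in the article: the microcautery-physiotherapy difference. It is treated as an assumption and varied.

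**Step 1: reproduce the stated figure.**
n = 2 × (1.96 + 0.84)² × 0.58² / 0.526² = 19.06, rounded up to 20 per group. The arithmetic is right for one pair. At n = 20 the two-sample t test has 79.8% power (81.8% by the normal approximation).

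**Step 2: the same pair under the planned analysis.**
- Standard error of a difference: 0.58 × √(2/20) = 0.183. Standardised effect: 0.526 / 0.183 = 2.87.
- Residual degrees of freedom: 3 × 19 = 57.
- Critical value on the t scale: 2.00 unadjusted, 2.41 for Tukey with three groups.
- Power for microcautery vs nasal oil with Tukey: about 68% (67% if the ANOVA must also be significant, with physiotherapy equal to nasal oil).

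**Step 3: microcautery significantly better than both.** Simulation of normal data with pooled variance, ANOVA then Tukey, and microcautery better than nasal oil by 0.526 throughout:

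| Assumed microcautery-physiotherapy difference | n per arm | Power to beat both |
|---|---|---|
| 0.526 | 20 | 53% |
| 0.263 | 20 | 16% |
| 0 | 20 | 1% (a false claim, since the two are equal) |
| very large | 20 | about 68% (limited by the nasal-oil pair) |
| 0.526 | 18 | 47% |

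The 18 is 20 × 0.9. It is an illustrative 10% loss, taken from the 10% mentioned for dropouts under Data Collection Plan and Management.

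**Step 4: where the loss comes from.** With both differences 0.526, power to beat both is 53% with or without the ANOVA gate, so the gate costs nothing once Tukey is used. The ANOVA itself is significant in 83% of trials, and exactly one of the two microcautery pairs is significant in 28%. If both contrasts had to succeed at unadjusted two-sided 5%, joint power would be about 70%.

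**Step 5: how often only the nasal-oil pair succeeds.** With ANOVA then Tukey, microcautery beats nasal oil but not physiotherapy in about 50% of trials if physiotherapy lies halfway between them. The figure is about 66% if physiotherapy equals microcautery.

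**The case against.** **The aims are a non-directional three-way comparison.** ANOVA with all-pairs Tukey is a conventional match to them. The directional hypothesis appears only in the Discussion, and the closing Conclusions describe the expectations as preliminary. This stands, and it is why the analysis should not be replaced. But the abstract also promises to find the most effective treatment, which requires one arm to beat two others, and the 68% for the single pair does not depend on the directional hypothesis at all.

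**The pairs are tested.** A reader might infer that the trial is decided merely by some group differing, or that an arm could be called best for having the highest mean after a significant ANOVA. The article does not support this: Statistical Methods goes on to pairwise tests, and nothing permits a claim from rank alone. What is missing is the pattern of pairwise results that supports the claim.

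**The 53% is conditional.** This also stands. A reader might take it as the trial's power, but it needs a physiotherapy difference of 0.526, which the article never states. Tukey is itself only an example, so every adjusted figure here rests on its being used.

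**Post hoc detail may be left to an analysis plan.** This is fair for naming contrasts. The 80%, however, is stated in the article and comes from a different test from the one the article specifies.

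**Conclusion.** The concern holds as a mismatch between the stated power and the planned analysis. The 20 per group is correct for one unadjusted comparison of microcautery with nasal oil. With ANOVA then Tukey, that pair has about 68% power. The joint claim has between about 1% and 68%, according to the unstated physiotherapy difference, and 53% if that difference is also 0.526. Under Tukey, no value of the physiotherapy difference restores 80%.

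These figures assume δ = 0.526 against nasal oil, SD 0.58, normal data with common variance, Tukey as the post hoc test and, except for the 18-per-arm line, no loss. For scale, with both differences 0.526, 80% joint power would need about 31 per arm (93 in total) under Tukey, or about 25 per arm (75 in total) if both contrasts had to succeed at unadjusted two-sided 5%.

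The documents do not support the stronger conclusion that ANOVA with Tukey is the wrong analysis.

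**What to change.** **Sample Size.** State the assumed microcautery-physiotherapy difference and its basis. In place of the 80%, give the power under the planned analysis, both for microcautery vs nasal oil and for microcautery beating both arms.

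**Statistical Methods.** Keep ANOVA and Tukey over all three pairs, and add wording such as: *A treatment, including microcautery under the study hypothesis, will be called the most effective only if it is significantly better than both other arms in the adjusted pairwise comparisons. If only one pair is significant, only that pairwise result will be reported.*

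**Alternative.** The sponsor may prefer to require both microcautery contrasts at unadjusted two-sided .05, with about 70% joint power when both differences are 0.526. Any claim from a single pair must then still use the multiplicity-adjusted P value: with all arms equal, at least one of the two unadjusted contrasts is significant in about 9% of trials. If this route also made physiotherapy vs nasal oil descriptive, it would narrow the three-way aim.

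**Cost.** The preferred fix changes wording only and needs no extra participants, visits or data. The stated power becomes less favourable.

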**Results:**

The results will be subjected to statistical analysis using appropriate methods such as ANOVA. If the ANOVA shows significance, post hoc tests (eg, the Tukey honestly significant difference test) will identify group differences, with *P*<.05 considered significant. As of January 2025, a total of 16 patients have been recruited, divided into 3 groups, and the final results are expected to be published in November 2025.

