#### Minimum Sample Size Required

Based on expected differences, variability, significance level, and power, the minimum sample size required was calculated to ensure reliable detection of a meaningful improvement:

n=1=2=2 × (1.96 + 0.84)^2^ × (0.58)^2^/(0.526)^2^=20 per group

Total samples = 20 × 3 per group=60

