### Randomization and Allocation

Computer-generated random numbers will be used to create a randomization chart. The participants will be randomized at a ratio of 1:1:1. To guarantee that treatment assignments are balanced, allocation sequence creation will be conducted using permuted blocks and provided in a randomized table. The researcher will enroll and give the participants an intervention and allocation sequence.

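### The 80% power is for one unadjusted two-group test; the planned ANOVA followed by Tukey has about 66-67% for microcautery versus nasal oil

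*Protocol article*

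**What the plan says.** Under Statistical Methods, "One-way ANOVA will be applied to compare the means of the 3 groups". The next step is conditional: "If ANOVA indicates a significant difference, post hoc tests will be further applied (eg, the Tukey honestly significant difference test"). The threshold is single: "A *P* value of <.05 will be considered statistically significant". The Results paragraph of the abstract repeats the sequence ("If the ANOVA shows significance, post hoc tests").

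The sample size rests on a different test. Formula Using Mean Difference is the two-group formula with 1.96 and 0.84, labelled as 5% error and 80% power. The difference is set for microcautery against nasal oil: "Considering 45% superiority in the thermal microcautery group=(1.17) × 45 = 0.526" (the multiplier is evidently 0.45, since 1.17 × 0.45 = 0.5265). The result is "n=1=2=2 × (1.96 + 0.84)^2^ × (0.58)^2^/(0.526)^2^=20 per group", multiplied by three arms to reach 60. Allocation is equal: "The participants will be randomized at a ratio of 1:1:1".

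Under Anticipated Findings the expected direction is stated: "Our hypothesis is that honey thermal microcautery will yield more effective results than standard physiotherapy and" nasal oil. No expected mean for physiotherapy is given anywhere.

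**The concern.** The value 1.96 belongs to a single two-group comparison tested at 5%. Under the analysis described, microcautery versus nasal oil counts as different only if the three-arm F test is significant and the pair then passes Tukey's larger critical value. Each condition lowers power, and the sample size calculation allows for neither.

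Readers of the protocol would take the trial to have an 80% chance of finding the assumed difference. If the real chance is nearer two in three, a null result is considerably more likely than advertised even if the assumption is right. The article itself lists the small sample as a limitation, so it matters whether some of this loss can be recovered without more participants.

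**Working it through.** **Inputs.** Difference 0.526 and SD 0.58 (Primary Variable: Abduction Improvement); 20 per arm (Minimum Sample Size Required); three arms, ANOVA, Tukey and P<.05 (Statistical Methods). Assumptions: normal data, SD 0.58 in every arm, complete data. The physiotherapy mean is not given, so it was varied.

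**1. The protocol's figure.** 2 × (1.96 + 0.84)² × 0.58² / 0.526² = 2 × 7.84 × 0.3364 / 0.2767 = 19.06, rounded up to 20. This reproduces. Power at 20 per arm by the same normal formula is 81.8%.

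**2. Critical values.** With three arms of 20 and pooled variance there are 57 degrees of freedom. The critical |t| is 2.002 unadjusted and 2.406 for Tukey.

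**3. Hand check.** The expected t for microcautery versus oil is 0.526 / (0.58 × √(2/20)) = 0.526 / 0.1834 = 2.868.
- Unadjusted, no ANOVA condition: Φ(2.868 − 2.002) = Φ(0.866), about 81% (simulation 80.5%).
- Tukey, no ANOVA condition: Φ(2.868 − 2.406) = Φ(0.462), about 68% (simulation 67.7%).

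Nearly all of the loss comes from the Tukey critical value.

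**4. Full procedures by simulation** (400,000 trials per scenario). Power for microcautery versus nasal oil:

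| Physiotherapy mean | ANOVA then Tukey | ANOVA then unadjusted pairs | Gain (points) |
|---|---|---|---|
| equal to oil | 67.3% | 76.0% | 8.7 |
| midway | 66.3% | 69.5% | 3.2 |
| equal to microcautery | 67.4% | 76.0% | 8.6 |

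Putting the ANOVA condition in front of Tukey costs only 0.4 to 1.4 points relative to Tukey alone.

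**5. Family-wise error, equal variances.**

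| Procedure | All three means equal | Two equal, third different |
|---|---|---|
| ANOVA then Tukey | 4.5% | about 1.9% |
| ANOVA then unadjusted pairs | 5.0% | 3.5% to 5.0% |
| Unadjusted pairs, no ANOVA | 12.1% | about 5% |

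The second row follows from the closed-test argument. With exactly three arms, once the global null is false at most one pairwise null can still be true. The 5% F test guards the global null, and the single 5% pairwise test guards the one that is left. The argument fails with four or more arms.

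**6. Family-wise error, unequal variances.** Take physiotherapy and oil as equal, both with SD 0.58, and microcautery far away with a smaller SD. The pooled SD is then too small for the physiotherapy–oil comparison. With microcautery SD 0.30 it is √((0.09 + 0.3364 + 0.3364)/3) = 0.504.

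| Microcautery SD | ANOVA then unadjusted pairs | ANOVA then Tukey |
|---|---|---|
| 0.30 | 8.8% | 4.1% |
| 0.40 | 7.4% | 3.3% |

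The distortion has a direction. If physiotherapy is the arm with SD 0.30, the figures are 3.4% and 1.2%.

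**7. Attrition.** With 18 per arm (20 less 10%) and physiotherapy equal to oil, power is about 62% for ANOVA then Tukey and about 71% for ANOVA then unadjusted pairs.

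**The case against.** ANOVA followed by Tukey is conventional and controls family-wise error. Tukey is introduced only as an example, so the pairwise method is not finally fixed, and a protocol article may leave that to an analysis plan. This stands as far as the choice of test goes: nothing in the article makes Tukey an error. It does not rescue the power figure. Of the procedures checked, only unadjusted pairs without the ANOVA condition reach about 80%. The article makes pairwise tests conditional on the ANOVA, and with that condition power is at most about 76% when physiotherapy lies between the other two arms.

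A reader might infer that Tukey after ANOVA corrects twice to no purpose and should simply be dropped. The documents do not support that. The gain depends on a physiotherapy mean that is never stated and can be as small as 3 points. The extra strictness does protect against error when SDs differ, and three very different treatments scored on a graded scale give no assurance that they will be equal.

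The control described above covers one outcome at one visit. The plan has four measures at three follow-up days, and neither procedure deals with that. Finally, if the claim is that microcautery beats both other arms and both comparisons must succeed, that joint claim needs no multiplicity adjustment. Unadjusted pairs after ANOVA is therefore one reasonable option, not the only one.

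**Conclusion.** The point holds as a mismatch between the sample size and the analysis. The arithmetic for 20 per arm is right for the test it assumes, but that is not the test planned. With the procedure as named, power for microcautery versus nasal oil is about 66-67%, some 13 to 14 points below the stated 80%. This rests on difference 0.526, SD 0.58 in all arms, 20 analysed per arm, and physiotherapy lying between the other two.

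The alternative pairwise step is valid for three arms with equal variances and recovers 3 to 9 points. It might be read as restoring the planned power. It does not: 69-76% is still short of 80%.

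**What to change.** **Needed.** Restate the power in the sample size section for the procedure that will be used: about 66-67% for microcautery versus nasal oil if it stays ANOVA followed by Tukey, with the assumed physiotherapy mean stated. This costs one or two sentences.

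**Optional.** Replace the example with a definite choice: unadjusted pairwise tests, carried out only if the three-arm F test has P<.05, and quote about 69-76%. This is one line and needs no extra participants. State with it that:
- the 5% control relies on there being exactly three arms and on equal variances, and covers one outcome at one visit;
- the pairwise confidence intervals are no longer simultaneous (Tukey intervals can be given as supportive);
- if the arm SDs differ, pair-specific Welch-type tests replace the pooled error term, or Tukey is kept.

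The choice should be fixed before outcome data are compared between arms. If 80% is wanted for either procedure, the sample size has to be recalculated for it.
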